### Dropout, Withdrawal, and Suspension Criteria

#### Dropout Criteria

Participants who develop SAEs will be withdrawn from the RCT after reporting to the Institutional Ethics Committee. Participants who develop concomitant diseases of viral origin during the trial that would affect the efficacy and safety assessment intervention, participants with poor compliance, those changing the intervention or adding therapy prohibited under the study for any reason, breaking the double-blind setting of the clinical trial, and those found to have any serious violations of the inclusion/exclusion criteria after enrollment will be withdrawn from the study.

#### Voluntary Withdrawal of Participants

The participant can become unwilling/unable to continue in the RCT and request the site PI to withdraw them from the RCT; other participants who stop visiting even after prompt reminders by the site PI will be withdrawn from the study. Every participant can withdraw from the trial anytime for any reason and without prejudice. Any participant who withdraws from the trial shall undergo a complete final examination, if possible, or at least a last telephonic interview at the time of withdrawal from the study about the state of their health by the investigator, and if necessary, from the point of view of drug safety and the validity of study results. The reason for the withdrawal will be recorded in the Participant Off Study form of the CRF.

#### Conditions for Trial Suspension

If any SAE occurs during the study, the trial will be terminated immediately as per recommendations of the DSMB and Ethics Committee. If there is a major error in the trial or a serious protocol deviation during implementation, which would make it difficult to evaluate the drug efficacy and safety, the trial will be stopped. The trial will also be terminated if the funding agency or collaborating institution requests to stop the trial or if the regulatory authority cancels the trial. The Council is entitled to terminate the trial prematurely at any time for medical and/or organizational reasons. This decision will generally be made based on the recommendations of the Scientific Advisory Board, CCRH, New Delhi, or the Director of Homoeopathy, Government of Kerala.

### Intervention Procedure

#### Preparation of Study Intervention and Placebo Materials

AA30CH will be prepared at [name] India Pvt Ltd, Noida, Uttar Pradesh, India (a licensed homeopathic drugs manufacturing company complying with Good Manufacturing Practice standards in India) as per the Homoeopathic Pharmacopoeia of India standards, using the active component of *Arsenicum album* in a fine powder mixed with glycerin, purified water, and pharmaceutical-grade ethanol following standard homeopathic drug manufacturing protocols approved by drug licensing authorities in India. The placebo (30CH) will be identically prepared using only glycerin, purified water, and pharmaceutical-grade ethanol, without the medicinal active component (*Arsenicum album*).

#### Interventions in Each Group

Following the second screening, participants with normal or borderline elevated values will be allocated to intervention and placebo arms as per the randomization sequence generated using the software PASS 2021 (v21.03). The intervention period for both groups consists of three schedules of 21 days each, with a total trial period of 66 days, including intervention, blood sample collection before and after the intervention, and three weekly telephonic follow-ups in each of the schedules. The sealed bottles of AA30CH and placebo 30CH dilutions will be opened at the in-house pharmacy of NHRIMH, Kottayam, under the supervision of the PI and the pharmacy in charge. Following standard pharmacy practice, these dilutions will further be used (approximately nine drops) for medicating one-grain lactose/sucrose (inert nonmedicated) tablets. Participants will be administered either the homeopathic medicine AA30CH or placebo as per the randomization sequence in three doses of single tablets orally for each of the 3 consecutive days of the 21-day schedule. Each of the three intervention schedules will be preceded and followed by a blood draw of the participants. The administered dose will be recorded in the Drug Dispensation Log of the CRF.

#### Criteria for Discontinuing or Modifying Allocated Interventions

All participants shall be advised to telephonically inform the site PI if they develop symptoms similar to COVID-19 infection. If any participant reports symptoms, the intervention shall be stopped, and if testing positive for COVID-19 in RT-PCR, the local health authorities will be informed by the site PI. Study participants shall be advised to take the treatment of their choice from the dispensary at the study site through teleconsultation or from other medical facilities nearby. In case of requirement, the study participants will also be provided support through an already allocated medical health insurance policy (valid for 1 year) for their hospitalizations or other related treatments. They shall be under observation in this study until their recovery from the symptoms and may report any events that may be an SAE. The site PI will record the days to recovery, disease stage, and severity of symptoms, among other clinical data. The details of treatment and progress will be acquired from family members or the participants themselves, which may be recorded in the follow-up and participant study forms in the CRF. A COVID-19–positive status with the intervention or placebo will be considered as the study endpoint for participants with a positive test result on RT-PCR.

#### Strategies to Improve Adherence to Intervention Protocols and Procedures for Monitoring Adherence

The participants must visit the study site for the 3 days of the intervention at each schedule. To ensure compliance, the independent dispenser will only administer the medicine and placebo to the participants at the prescribed dosage. The intervention procedure will be under the supervision of the site PI to ensure adherence. Any deviation in these procedures will be recorded in the Deviation/Unanticipated Problem Tracking Log of the CRF. Participants will be under observation of the site PI at the study site for at least 1 hour to monitor for any immediate drug-related adverse effects, which will be recorded and informed to the PI. If the participant feels any discomfort, they will be medically examined by the site PI. Vital parameters such as heart rate, respiratory rate, and blood pressure will be monitored and recorded. In case of any SAE, the participant will be referred to a tertiary-care facility after receiving appropriate first aid at the site by the site PI. The DSMB and Ethics Committee will be duly informed about these events. Blood samples will be drawn and stored 1 day before and after 3 days of the intervention and on the last day of the study by the designated laboratory involved in sample collection and storage. During each visit, participants will be compensated for travel from their home to the study site and provided with protein-based refreshments to minimize their difficulty at each visit to the study site, thereby improving adherence.

#### Relevant Concomitant Care and Interventions Permitted or Prohibited During the Trial

Any medical problem a participant faces during the trial period will be informed to and managed by the site PI of the study site appropriately and documented and reported to the PI. The administration of vaccinations is not permitted during the study duration as it would interfere with the study results. If a participant is taking immunosuppressants, hormonal therapies, or any other Ayush therapies for chronic ailments, they will be considered a dropout. If the participant reports the intake of any other concomitant medications not specified in the exclusion criteria, the same may be documented in the Concomitant Medication Log of the CRF.

### Outcome Measures

The primary outcome measures of the study are the estimation of antigen density and modulation in immunological markers (CD3, CD4, CD8, CD24, CD27, CD38, CD4 IFN-γ, CD4 CD17, CD4 CD25 [activated T lymphocytes], T cells, B cells, DCs [mature and immature], and NK cells) observed from the blood sample drawn 1 day before and after 3 days of the intervention (ie, on days 1, 5, 23,27, 45, and 49) and at the end of the study (day 66), along with the innate and acquired immune responses from the blood sample drawn on days 1, 23, 45, and 66 of the study interventions.

The secondary outcome measures of the study are to evaluate the toxicity status of study participants who have taken AA30CH or placebo based on hepatic, renal, and hematological parameters and peripheral smears 1 day before and after 3 days of the intervention (ie, on days 1, 5, 23, 27, 45, and 49) and at the end of the study (day 66); the number of participants developing COVID-19–like symptoms as per NCDC guidelines during follow-ups in any of the three intervention schedules; and the number of participants with COVID-19–like symptoms who test positive for RT-PCR during follow-ups in any of the three intervention schedules.

### Participant Timeline

The study consists of three schedules of 21 days each. Each participant will have seven blood draw visits (V2, V6, V7, V11, V12, V16, and V17) during the study period. The blood samples will be drawn for conducting LFTs, RFTs, CBC, and peripheral smears 1 day before and after 3 days of the intervention (ie, on days 1, 5, 23, 27, 45, and 49) and at the end of the study (day 66) (Table 1, Figure 2).

**Table 1 table1:** Participant visits (V) for the three schedules with the telephonic follow-up (T) timeline.

Procedures	Baseline		Schedule 1					Schedule 2					Schedule 3			
	V0	V1	V2	V3-V5	V6	T1-T3	V7		V8-V10	V11	T1-T3	V12		V13-15	V16	T1, T2, V17
Consent	✓															
RT-PCR^a^ test		✓														
Enrollment, randomization, and first intervention				✓^b^												
Blood sample collection for immunological assays (PBMCs^c^), innate and acquired immune responses, LFT^d^, RFT^e^, CBC^f^, peripheral smear			✓		✓		✓			✓		✓			✓	✓
Intervention (AA30CH^g^ or placebo)				✓					✓					✓		
Follow-ups						✓					✓					✓

^a^RT-PCR: reverse transcription-polymerase chain reaction.

^b^At V3 only.

^c^PBMC: peripheral blood mononuclear cell.

^d^LFT: liver function test.

^e^RFT: renal function test.

^f^CBC: complete blood count.

^g^AA30CH: *Arsenicum album* 30CH.

**Figure 2 figure2:**
[figure not shown]
Flow diagram of three schedules of intervention (21 days each). RT-PCR: reverse transcription-polymerase chain reaction; T: telephonic follow-up; V: visit.

### Adverse Events

Any SAE that occurs during and after the study period and is possibly considered due to the study intervention or participation will be recorded and reported immediately to the concerned ethical committee and DSMB.

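### The Adverse Events rule ties recording and DSMB reporting of an SAE to suspected relatedness, which conflicts with other sections, and the plan is ambiguous on whether an SAE ends the trial

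*Protocol article*

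**What the plan says.** All references are to the Methods of the protocol article.

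**Recording and reporting**
- *Adverse Events* consists of one sentence. An SAE during or after the study period that "is possibly considered due to the study intervention or participation will be recorded and reported immediately"; the recipients it names are the ethics committee and the DSMB.
- *Strategies to Improve Adherence* requires at least one hour of observation at the site "to monitor for any immediate drug-related adverse effects, which will be recorded and informed to the PI". It then says "In case of any SAE, the participant will be referred to a tertiary-care facility after receiving appropriate first aid at the site", and that "The DSMB and Ethics Committee will be duly informed about these events".
- *Relevant Concomitant Care* says "Any medical problem a participant faces during the trial period will be informed to and managed by the site PI", with documentation and a report to the PI.
- *Data Monitoring and Management* has the laboratory safety data submitted to the DSMB after each of the three schedules.

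**Consequence of an SAE**
- *Dropout Criteria*: "Participants who develop SAEs will be withdrawn from the RCT after reporting to the Institutional Ethics Committee".
- *Conditions for Trial Suspension* gives the rule at trial level: "If any SAE occurs during the study, the trial will be terminated immediately as per recommendations of the DSMB and Ethics Committee".
- *Randomization and Blinding* allows unblinding after an SAE if the DSMB or ethics committee recommends it.
- *Criteria for Discontinuing or Modifying Allocated Interventions* keeps participants with COVID-19-like symptoms under observation until recovery, during which they may report possible SAEs.

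**The concern.** Whether an event is possibly related is an opinion formed on a single case. A DSMB exists partly to see imbalances between arms that no single case reveals, and for that it needs all SAEs, whatever the first opinion on cause. A rule that asks for the opinion before the event is recorded and sent on can keep an unexpected harm from the body meant to detect it. Safety is a stated aim of this trial, so this matters even though SAE counts are not a listed outcome.

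The second issue is that the same trigger, an SAE, has one consequence for the participant in one section and another for the whole trial elsewhere. If termination is automatic, a single event stops the trial. If it is discretionary, the wording does not say so cleanly. Neither consequence carries a relatedness condition, although the recording rule does.

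**Working it through.** The plan states no SAE figure to reproduce. The check is mainly a comparison of the text, with one illustrative calculation.

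**Step 1: which rule sends an SAE to the DSMB?**

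| Section | Relatedness needed? | Who is told | Setting |
|---|---|---|---|
| Adverse Events | Yes | Ethics committee and DSMB | Any, during and after the study |
| Strategies to Improve Adherence | No for SAEs | DSMB and Ethics Committee | Follows the on-site observation and first aid at the site |
| Relevant Concomitant Care | No | PI | Any, during the trial |
| Dropout Criteria | No | Institutional Ethics Committee | Any |
| Data Monitoring and Management | Not applicable | DSMB | Laboratory parameters only |

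The only unconditional route to the DSMB for an individual SAE stands in the text on dosing visits. Dosing takes 3 days in each of 3 schedules, so 3 × 3 = 9 days. The 7 blood draws fall on other days. That makes 9 + 7 = 16 site-visit days out of 66, and 66 − 16 = 50 days with no site visit. For an SAE at home on one of those days, *Adverse Events* is the only section that expressly sends it to the DSMB, and only if it is thought possibly related.

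**Step 2: does this touch the planned safety comparison?**

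*Outcome Measures* and *Statistical Analysis* define that comparison through hepatic, renal and hematological parameters and peripheral smears at seven scheduled draws in both arms. No causality judgement enters, so it is not affected.

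**Step 3: participant or trial?**

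*Dropout Criteria* and *Conditions for Trial Suspension* start from the same event. If the second is automatic, the first has little separate purpose. If it depends on committee recommendations, the two can coexist, but the sentence combines an immediate consequence with a recommendation and gives no criteria. *Criteria for Discontinuing or Modifying Allocated Interventions* adds a further tension: a participant whose COVID-19-like illness becomes an SAE would be both kept under observation until recovery and withdrawn.

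**Step 4: how often could this arise? (illustration only)**

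Inputs: planned enrolment of 224 (*Sample Size*) and an assumed SAE risk p per participant over the 66 days, independent between participants. The chance of at least one SAE is 1 − (1 − p)^224.

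| Assumed p | Expected SAEs, 224 × p | Chance of at least one |
|---|---|---|
| 0.1% | 0.22 | 1 − 0.999^224 = 20% |
| 0.25% | 0.56 | 1 − 0.9975^224 = 43% |
| 0.5% | 1.12 | 1 − 0.995^224 = 67% |
| 1% | 2.24 | 1 − 0.99^224 = 89% |

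These figures show how likely it is that the SAE rules are called on at all. They do not measure how many events the relatedness condition would lose; nothing in the article allows that to be calculated.

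**The case against.** A reader might infer three stronger things, and the document does not support them.

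1. *Only related SAEs are ever recorded.* The *Adverse Events* sentence does not contain that word. Medical problems of any cause are documented and reported to the PI, SAEs at the site are notified to the DSMB, and SAE withdrawals follow a report to the ethics committee. This stands: the defect is a conflict between sections, not a total loss of unrelated events.
2. *The safety comparison is biased by opinion.* The planned comparison is of scheduled laboratory measures and has no causality filter. The site PIs are stated to be blinded, which limits any filtering that differs by arm. This stands too.
3. *Continuation of the trial is undefined, or one unrelated admission must end it.* The suspension rule names the DSMB and Ethics Committee as the bodies whose recommendations count. Withdrawal of a participant and termination of a trial are also different levels and can both apply. The wording is therefore ambiguous, not empty.

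It is also fair to say that an article condenses a fuller protocol. *Pretrial Preparation* mentions standard operating procedures and case record form booklets that are not shown, and these may hold definitions, causality fields and DSMB criteria. That would answer a complaint about missing detail. It does not answer this one, which concerns a condition the article states and wording in other sections that does not match it.

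**Conclusion.** The point holds in a limited form. *Adverse Events* makes recording and immediate DSMB and ethics reporting of an SAE conditional on possible relatedness, against unconditional wording in three other sections. Followed as written, an off-site SAE judged unrelated need not reach the DSMB. This rests on reading the unconditional DSMB notice in *Strategies to Improve Adherence* as applying to events at the site, which is how its context presents it. On the broadest reading of that sentence, the sections still contradict each other.

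Separately, the text can be read as automatic or discretionary termination of the trial after an SAE, alongside a rule that withdraws the participant. At the assumed risks of 0.1% to 1%, the chance that the question arises is 20% to 89%; the range depends wholly on those assumptions.

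What is at stake is the capture of clinical events and DSMB oversight, not the laboratory comparison.

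**What to change.** - Delete the relatedness condition in *Adverse Events*, so that every SAE is recorded and reported to the ethics committee and DSMB. Keep the window already stated, which includes the time after the study period; do not shorten it to day 66.
- Record causality as a separate field, assessed blind to arm.
- Report SAEs of any cause by arm. *Results* says enrolment was complete by April 3, 2023, so for events that have already occurred, recover those judged unrelated from the medical-problem documentation required under *Relevant Concomitant Care*.
- The sponsor, DSMB and Ethics Committee must reconcile *Randomization and Blinding*, *Dropout Criteria*, *Conditions for Trial Suspension*, *Criteria for Discontinuing or Modifying Allocated Interventions*, *Strategies to Improve Adherence*, *Relevant Concomitant Care* and *Adverse Events*, so that they agree on what an SAE means for the participant and for the trial. No clinical rule is proposed here.

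The cost is a change of wording and slightly more case record form entry and reporting. No extra visits or participants are needed.

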### Data Monitoring and Management

The PI will monitor the study regularly, and site visits/online meetings will be held periodically on intervention and blood draw days. The PI will allocate adequate time for such monitoring activities and ensure that the monitor or other compliance or quality assurance reviewer can access all the study-related documents and study-related facilities (eg, pharmacy, diagnostic laboratory). The original records of participants (including CRFs, consent forms, follow-up forms, and laboratory reports) will be maintained at the study site by the site PI. These records will be reviewed during the scheduled monitoring visits by the PI to ensure compliance. The site PI will be responsible for the completeness and accuracy of the study materials and the nodal site PIs will check these during their visits to the study sites. Any observations/corrective measures required will be duly communicated to the site PIs for compliance. These records will be sent to the PI at CCRH headquarters after the completion of the study or as per the requirement of the study. The data of the laboratory parameters that indicate the safety aspects of the drug will be evaluated at the end of each of the three schedules. They will be presented/submitted to the DSMB for their recommendations. The data will be analyzed after completion of the study.

### Statistical Analysis

Data analysis will be performed following the intention-to-treat/per-protocol method. The safety and immunological parameters will be analyzed at each of the seven time points and comparisons will be made between the subjects and groups. Additional analyses (eg, subgroup analyses according to age, sex, and perceived risk categories) will also be performed based on the evolving trends from the analysis. A trial statistician will be engaged for the statistical analysis of the clinical trial.

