### Sample Size

The study is aimed at evaluating the immunologic responses of AA30CH. The study is based on earlier encouraging leads provided through community studies on the role of AA30CH in preventing COVID-19. Several parameters are in consideration for the evaluation of immunogenic responses. With regard to the computation of sample size, based on the literature and expert opinions, it is proposed to consider some limited immunologic parameters that are more relevant. Owing to the scarce availability of literature, it would be quite challenging to hypothesize the assumption. Assuming a type 1 error of 5% and a power of 80%, it was estimated that there would be 93 participants each in the intervention and control groups, with a total of 186 participants. This could be escalated based on attrition due to loss in follow-up. If this loss to follow-up is considered at 20%, a total of 112 participants have to be enrolled in each group, with a total sample of 224 that would need to be recruited for the study.

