### Screening and Enrollment

All the participants will be voluntarily invited to the study and then required to sign an informed consent form containing information on the regulatory authorities and related procedures, including initial RT-PCR screening, laboratory screening, and subsequent randomization after enrollment. The RT-PCR test will screen the participants fulfilling the eligibility criteria for an ongoing COVID-19 infection. If the RT-PCR test result is found to be negative for COVID-19, the participant will be investigated for an initial (baseline) LFT, RFT, CBC, and peripheral blood smear as part of the second screening for any abnormal parameters. Those with borderline elevated or normal values will be enrolled in the trial, followed by randomization. Screened participants with positive RT-PCR reports for COVID-19 will be notified to the local health authorities. Their health status will be telephonically monitored during quarantine or hospital stay by the site PI. Each study site will maintain a log register that records all details of the screened participants and the reason(s) for exclusion. Enrolled participants will then be randomized and allocated to the intervention or the placebo arm as per the generated randomization sequence using PASS software version 21.03.

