### Assessment, Data Analysis, and Manuscript Preparation

The laboratory parameters recorded during the seven blood draws of each participant will be analyzed for any statistically significant changes using appropriate statistical tests. The PBMCs isolated during the seven blood draws and stored in the –80°C freezer will be transported as air freight in liquid nitrogen tankers to DBT-THSTI, Faridabad, for immunological assays and data analysis. The interim reports will be confidentially submitted to the designated DSMB, internal committees of CCRH, and Ministry of Ayush, Government of India, on availability as per requirements. Manuscripts with the study findings will be prepared and submitted to Scopus-indexed peer-reviewed journals. Patents pertaining to this RCT will be filed as per the directions of the Ministry of Ayush, Government of India.

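### Day 1 is drawn before randomisation but is listed as one of seven equal analysis time points; it should be the baseline covariate, with no between-arm test at day 1

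*Protocol article*

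**What the plan says.** The Statistical Analysis section of the protocol article says that safety and immune parameters "will be analyzed at each of the seven time points and comparisons will be made between the subjects and groups". It names no model and no covariate, and it leaves the analysis to a trial statistician.

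Outcome Measures and Participant Timeline give the seven days as 1, 5, 23, 27, 45, 49 and 66. Table 1 puts the first blood draw at V2 and ticks "Enrollment, randomization, and first intervention" at V3 only. Screening and Enrollment gives the same order for the safety laboratory tests: baseline values are obtained first, and then "Those with borderline elevated or normal values will be enrolled in the trial, followed by randomization".

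Assessment, Data Analysis, and Manuscript Preparation adds: "The laboratory parameters recorded during the seven blood draws of each participant will be analyzed for any statistically significant changes using appropriate statistical tests". It does not say whether those changes are to be compared between arms.

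For the innate and acquired immune responses (the gene array), Outcome Measures names four days only: 1, 23, 45 and 66.

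**The concern.** The article does more than leave the model open. It states a structure, analysis at each of seven time points, and makes no exception for day 1. That matters in three ways.

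- **Day 1 as an outcome.** No arm exists when the day 1 sample is drawn. With sound randomisation, any difference between arms on that day is chance. Reporting a test there invites readers to treat a chance imbalance as a finding, or to discount later results because of one.
- **Lost precision.** Each participant supplies a day 1 value for each marker. If later comparisons ignore it, variation between people that it could explain stays in the error term, and any chance day 1 imbalance carries into the later estimates in proportion to the correlation.
- **Change with no stated comparator.** A search for significant changes over a participant's own draws can find time trends, assay drift or regression to the mean, none of which is an effect of the intervention. The day 23 and day 45 samples precede a dosing block but follow earlier dosing, so only day 1 is an untreated baseline.

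**Working it through.** **1. Order of events**

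| Day | Visit (Table 1) | Position |
|---|---|---|
| 1 | V2 | before randomisation and first dose (V3) |
| 5 | V6 | after first dosing block |
| 23, 27 | V7, V11 | after randomisation |
| 45, 49 | V12, V16 | after randomisation |
| 66 | V17 | end of study |

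One of the seven points precedes randomisation and six follow it.

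**2. What a day 1 test can yield.** The null hypothesis of no treatment effect is true there by design, so each test at 5% rejects about 5% of the time. Outcome Measures lists 14 cell markers if mature and immature dendritic cells are counted separately. The expected number of false positives at day 1 is 14 × 0.05 = 0.7, whatever the correlation between markers.

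**3. The plan's own sample size.** Sample Size gives a 5% type 1 error, 80% power and "93 participants each in the intervention and control groups, with a total of 186 participants". It states no effect size, SD or sizing parameter; it says instead: "Owing to the scarce availability of literature, it would be quite challenging to hypothesize the assumption". The 93 therefore cannot be reproduced forwards. Solving backwards, with a two-sided test assumed:

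d = (z₀.₉₇₅ + z₀.₈₀) × √(2/93) = (1.960 + 0.842) × 0.1466 ≈ 0.411

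A t-based calculation gives 0.413, and a one-sided test would give 0.365. This d is implied by the 93; the article does not state it as a planned effect.

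**4. Adding day 1 as covariate.** Let ρ be the correlation between day 1 and the later visit (not given, so assumed). The residual SD is multiplied by √(1 − ρ²), so at 93 per arm:

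power = Φ(2.802/√(1 − ρ²) − 1.960)

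The number per arm needed for 80% power is 93 × (1 − ρ²), rounded up. For a between-arm comparison of change scores, the SD factor is √(2(1 − ρ)).

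| ρ (assumed) | Later visit alone | Day 1 as covariate | Change score | n per arm for 80%, adjusted |
|---|---|---|---|---|
| 0.2 | 80.0% | 81.6% | 60.1% | 90 |
| 0.3 | 80.0% | 83.6% | 65.8% | 85 |
| 0.5 | 80.0% | 89.9% | 80.0% | 70 |
| 0.7 | 80.0% | 97.5% | 95.1% | 48 |

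Worked line for ρ = 0.5: 2.802/0.866 = 3.235; 3.235 − 1.960 = 1.275; Φ(1.275) = 89.9%.

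The gain is small at low correlation and large only from about 0.5. Covariate adjustment is ahead of the change score in every row. The change score is worse than ignoring baseline when ρ is below 0.5.

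**The case against.** The strongest reply is that the article is a short summary and that model and covariates normally sit in an analysis plan, which is not shown. That is right as far as it goes. A reader might infer that the trial has chosen separate comparisons instead of baseline adjustment. The text does not support this: it names no model, and nothing in it excludes a covariate or a repeated-measures analysis. Nor does it state outright that the arms will be tested against each other at day 1; the day 1 analysis could be a baseline summary.

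A reader might also infer that conclusions will rest on uncontrolled before-after change. That is not shown either. Comparison between groups is stated, and the sentence about changes is silent on the comparator.

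Regression to the mean is a further tempting argument, because entry depends on the screening laboratory values. It reaches only the liver, renal and blood-count values, which are secondary outcomes. It should affect both arms alike, so it does not bias the randomised comparison. It could mislead only a within-arm reading. Chance imbalance at day 1 likewise costs precision but does not invalidate an unadjusted test, whose error rate already allows for it.

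The narrower point stands. The article does fix a per-time-point structure that treats a pre-randomisation sample like the six later ones, and it leaves participant-level change without a between-arm contrast. That is a weakness in the wording itself and is more than missing detail.

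**Conclusion.** The point holds as a correction to the stated analysis structure. Day 1 is a baseline by the trial's own visit schedule, and the text should use it as one. The documents do not show an invalid analysis, a refusal to adjust, or conclusions built on before-after change.

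The size depends on two assumptions: d of about 0.41, back-solved from 93 per arm with a two-sided 5% test and 80% power, and a baseline correlation for which the article gives no figure. Over correlations of 0.2 to 0.7, power at one post-baseline visit moves from 80% to between about 82% and 97.5%. The correlation may differ by marker and by visit. The benefit could be slight for some outcomes, but in a trial of this size the covariate costs almost nothing even then.

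The change is worth making because it is nearly free. The article reports enrolment complete with the immunological assays still to come, and it places data analysis after study completion, so as the article describes matters the wording could be settled before the immune results are seen.

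**What to change.** Replace the per-time-point sentence, and align the sentence on changes over the seven draws, with wording such as:

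> Day 1, drawn before randomisation, is the baseline. For each parameter, the arms will be compared at post-baseline visits with the day 1 value as covariate, by ANCOVA or a repeated-measures model. Post-baseline visits are days 5, 23, 27, 45, 49 and 66 for cell markers and laboratory values, and days 23, 45 and 66 for the gene array. Day 1 values will be summarised by arm without a between-arm test. Change within an arm is descriptive and will not be used to infer efficacy or toxicity.

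The separate visit lists are needed because Outcome Measures ties the gene array to four days only. The choice between ANCOVA and a repeated-measures model, the scale for skewed markers and any further covariates can stay with the analysis plan.

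Cost: analysis wording only. Every sample required is already in the Table 1 schedule, so no visit, assay or participant is added. If the protocol text itself is amended, the Protocol Amendments section limits amendments to exceptional cases and requires ethics committee approval and notification of the trial registry. Putting the wording in the analysis plan before the immune data are examined would achieve the same end.
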